## Abstract

**Background/Objectives**: Chronic diseases account for 74% of global deaths, with multimorbidity (existence of more than one chronic condition) increasing disability risk and treatment burden, leading to poor adherence, disease progression, and reduced quality of life. Nursing-led proactive care models that focus on patient engagement, education, and self-care can help mitigate these challenges. The study aims to evaluate the effectiveness of a nurse-led proactive health intervention in improving care for individuals with chronic diseases in general practice. **Methods**: A quasi-experimental pre–post study will be conducted in a Community Health Home in Northern Italy. Family and community nurses will deliver the intervention, which includes assessments, educational sessions, and follow-ups for patients aged 65+ with at least one chronic condition. Recruitment will occur over three months. **Results**: Primary outcomes include emergency department visits and hospitalizations, while secondary outcomes focus on medication adherence, self-care, and service utilization. Data will be collected at 6 and 12 months, and statistical analysis will use descriptive methods and generalized estimating equations (GEEs). **Conclusions**: This study will improve the understanding of the value of nurse-led proactive intervention, filling the gap in the literature by testing evidence-based approaches on a realistic frail population. Moreover, delivering a complex but structured intervention will provide evidence for future interventions to reduce treatment burden and improve health outcomes.

## 1. Introduction

Population aging and socio-environmental changes have globally led to an increase in conditions like hypertension, overweight, obesity, and physical inactivity, identified as significant risk factors for the development of long-term diseases and potentially fatal acute events [1]. Chronic diseases are responsible for nearly 74% of global deaths [1]. In addition, multimorbidity significantly increases the risk of disability [2]. Nonetheless, multimorbidity can lead to a treatment burden, which, in turn, can result in non-adherence to treatment, disease progression, poor health status and quality of life, and caregiver burden [3]. These consequences of chronic diseases call for interventions to prevent and reduce multimorbidity and the related treatment burden by promoting proactive care for community-dwelling people [3]. These proactive health interventions involve engaging with populations, communities, families, and individuals to foster empowerment and self-care skills, defined as the ability of individuals, families, and communities to promote health, prevent disease, maintain health, and cope with illness and disability. Proactive healthcare has been widely promoted and implemented internationally, primarily through the development and adoption of innovative community and primary care models, such as the Chronic Care Model [4]. This model comprises six components: a proactive care approach that promotes patient engagement and the development of empowerment skills; the involvement of community resources; structural changes within healthcare organizations; the implementation of multidisciplinary teams; and the use of digital systems to support patient care [5]. This is supported by evidence-based decision-making and a patient-centered care model [4]. The model has been widely applied in primary care and is considered the first element of a continuous care process and the first point of contact for individuals, families, and communities within Campo’s healthcare system [6]. The World Health Organization supports the development of these types of models and their global spread. Indeed, the Alma-Ata Declaration in 1978 and the renewed Astana Declaration in 2018 [7] emphasize the importance of primary care to promote sustainable prevention and proactive health interventions, thereby reducing the occurrence of multimorbidity and disability. In this context, the nursing role is crucial for proactively and effectively responding to the needs of individuals, families, and communities through interventions focused on prevention, health promotion, and education [8,9]. Various systematic reviews highlight the effectiveness of nurse-led care models in primary care, reporting significant improvements in treatment adherence, self-care, self-efficacy, quality of life, and reduced incidence of complications [10,11,12]. These models have primarily been studied in specific population groups, involving frail individuals [13] with chronic conditions such as COPD [14], hypertension, diabetes, and cardiovascular diseases [15,16,17], as well as those exposed to risk factors like smoking habits [18]. Therefore, although a substantial body of literature demonstrates the effectiveness of nurse-led care models in primary care settings, there is no evidence on the impact of proactive nursing care on specific conditions in primary care. This could provide evidence of a nurse-led intervention that is adequate across various chronic conditions, improving outcomes for individuals with multiple chronic conditions while assessing its effect on particular multimorbidity patterns [3].

Therefore, this study aims to evaluate the effectiveness of a nurse-led, proactive health intervention focused on educational care for individuals with chronic diseases in primary care.

## 2. Methods

### 2.1. Study Design and Setting

A quasi-experimental pre–post study will be conducted in a Community Health Home in a rural district in the North of Italy with a population of 15,917 citizens, served by one local hospital. The Community Health Home is a recently introduced service in Italy, mandated by the National Law, to improve the quality of primary care. It includes different professionals within the same community structure, such as general practitioners, specialist physicians, social workers, and other allied health professionals, as well as home care nursing services and family and community nursing services. Specifically, this study directly involves this last group of professionals. Family and community nurses will deliver a structured educational intervention to outpatients with chronic diseases, aiming to reduce unhealthy lifestyles and harmful health behaviors and to promote health in the community. In the Community Health Home setting of the study, two family and community nurses with a Master of Science in primary care work from 7.00 a.m. to 3.00 p.m.

The study has been registered with the number NCT07479810 on https://clinicaltrials.gov/ (accessed on 18 March 2026).

### 2.2. Population

We will include all patients over 65 years old, assigned to general practitioners in the district of reference of the Community Health Home, diagnosed with at least one non-oncological chronic condition. Exclusion criteria are a life expectancy of less than 12 months, as assessed by the general practitioner, and an active plan for intensive home care (more than one home access/week). Potential participants will be referred by general practitioners, social workers, or other professionals from home care, community, and transitional care services to family and community nurses (hereafter, nurses). They will ascertain the inclusion criteria and collect informed written consent to participate in the study. Patients assigned to nurses will be recruited through consecutive sampling. It is not possible to perform an a priori power analysis because no data are available on the composite primary endpoint. However, using empirical data collected in the same setting and by estimating a difference between pre and post evaluations consistent with that observed in other similar studies [19,20], we aim to enroll 100–120 patients. Considering this information and the usual caseload of eligible users, the researchers have set a 3-month enrollment period.

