
### 2.5. Outcomes

The primary clinical outcome will be a composite of at least one event, including emergency department visits or hospitalization for related pathological causes. This outcome will be evaluated pre- and post-intervention to assess the effectiveness of the proactive care on hard endpoints. On the other hand, secondary outcomes will be assessed after the intervention in terms of the following:Medication adherence through the calculation of the periods elapsed between prescriptions;Self-care ability assessed using the Patient Activation Measure (PAM) [41];Quality of received care by Patient-Reported Experience Measurement (PREMsT questionnaire).

The following process evaluations will also be collected during the reference period:Number of patients with periodic use of the nursing service (at least three visits);Number of nursing visits for each user;Number of nurse visits at home;Number of users that received structured family assessment interviews;Number of medical visits by the general practitioner for each user;Rate of users with new prescriptions of aids/devices;Number of services activated per person: physiotherapist, palliative care, social worker, etc.;Rate of users reported to the general practitioner for suspected exacerbation of chronic pathology.

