### 2.6. Data Collection

All data needed for the analysis, meaning outcome measures, socio-demographic data, and assessment evaluations, will be computed pseudonymized in a different Excel file, secured by the research network. Information will be collected from nurses’ Excel charts and databases already in use by the pharmacy service and hospital facilities. The region shares an integrated electronic database that provides access to data from all surrounding facilities. Data collection will be carried out for the primary outcome over 12 months before and over 12 months after enrollment, and for secondary outcomes through 6 and 12 months following enrollment (Table 1). Specifically, questionnaires on self-care and the quality of received care will be administered at three time points: enrolment, 6 months, and 12 months. To establish the correlation between hospitalization and patients’ underlying chronic diseases, hospital discharge records, IDC codes, and discharge summaries will be assessed. When ICD codes do not specifically refer to “exacerbation” or “acute on chronic” or “decompensated” condition, the discharge letters will be analyzed, searching for the same information. When these criteria are not met, hospitalization will be considered generic, and two GPs will be involved to assess the correlation; any disagreement will be resolved through discussion.

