## 3. Limitations and Transparency

This study, like many other pre–post studies, lacks a counterfactual comparison group [42,43], leaving the outcomes exposed to uncontrolled confounders and secular trends. The chosen design aims to assess the pragmatic effectiveness of a nurse-led proactive health intervention in a real-world setting. Health Community Homes are a newly established reality in Italy, designed appropriately to provide the best care for fragile patients. The eligible population and the number of users employed in this setting are nowadays specifically tailored for intercepting and designing new models to care for the elderly with almost one chronic pathology. For these reasons, using a different care facility or primary healthcare professional to provide a comparison is unfeasible. Even if the study employs a double follow-up period and logistic regression to assess confounders, this remains a major limitation for making inferential conclusions. Moreover, the study lacks a justification for the sample size. The selection of this composite endpoint is meaningful in practice, but it does not improve statistical power evaluations. The lack of formally available data makes it impossible to compute a formal sample size, even for the most frequent outcome. Although some evaluations on the cusp of statistical acceptability have been conducted, the researchers prefer not to define this as an a priori power analysis due to its poor reliability. Thereby, they chose to statistically underestimate future results to preserve the study’s informational value [44,45]. Nevertheless, post hoc power analysis would have been subject to excessive variability [46] and would not be helpful overall. Given the risk of type II error, there is no ambition to make inferential conclusions. The focus of this project is on the true value of nursing interventions, so *p* values can be considered less meaningful than other measurements [47]. Taking this into account, the results will cautiously discuss the effect size observed alongside the process evaluations of the intervention, aiming to provide policymakers with useful information on the early introduction of Community Health Homes and Family Nursing.

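### The pre-window ends at enrolment and entry is by referral, so the uncontrolled primary comparison is exposed to regression to the mean towards apparent benefit, of unknown size

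*Protocol article*

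**What the plan says.** - **Outcome (2.5):** "The primary clinical outcome will be a composite of at least one event, including emergency department visits or hospitalization for related pathological causes".
- **Windows (2.6):** "Data collection will be carried out for the primary outcome over 12 months before and over 12 months after enrollment". The two windows meet at enrolment, and no gap is described.
- **Entry (2.2):** "Potential participants will be referred by general practitioners, social workers, or other professionals from home care, community, and transitional care services". The other conditions are age over 65 and being "diagnosed with at least one non-oncological chronic condition". No recent acute event is required. On sampling: "Patients assigned to nurses will be recruited through consecutive sampling".
- **Analysis (2.8):** McNemar's and Wilcoxon's tests for pre against post, GEE models adjusted for baseline confounders, and significance at p < 0.05. Sensitivity analysis is something the researchers will consider.
- **Limitations (3):** the study "lacks a counterfactual comparison group", "leaving the outcomes exposed to uncontrolled confounders and secular trends". The authors disclaim inferential conclusions but will discuss the observed effect size for policymakers. Regression to the mean and selection on recent events are not mentioned.

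**The concern.** Referral by a professional is usually prompted by need, and transitional care services see patients around discharge. If a related ED visit or admission prompts the referral, that event falls in the 12 months before enrolment and makes the pre-period positive. The post-period starts at enrolment with no such condition attached. A group selected this way tends to show fewer events afterwards, whatever the nurses do.

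This bias has a direction: it favours the intervention. It also acts on the effect size itself, which is the quantity Section 3 intends to put before policymakers. Playing down p values therefore gives no protection.

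**Working it through.** **Inputs from the article.** One group; binary composite; 12 months before and after enrolment with no gap; McNemar's test at 0.05 (two-sided assumed); "we aim to enroll 100–120 patients". The enrolment target cannot be reproduced, because no event rate, effect size or power is given. It serves here only as the sample size.

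**Assumptions, not in the article.** The share *s* of patients enrolled because of a qualifying event; the event risk or rate; its spread between patients. The true effect is set to zero throughout.

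**Step 1: closed form.** Let *p* be the true 12-month risk, the same before and after. Triggered patients are positive before enrolment.

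- Pre = s + (1−s)p. With equal risk for all, post = p and the fall = s(1−p).
- With exponentially distributed rates, and triggered patients weighted by their rate, the fall = s(1−p)².

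Example with p = 0.30 and s = 0.20:

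- Equal risk: pre = 0.20 + 0.80×0.30 = 0.44; post = 0.30; fall = 14 points.
- Discordant pairs, event before only: 0.20×0.70 + 0.80×0.30×0.70 = 0.308. Event after only: 0.80×0.30×0.70 = 0.168. Ratio 1.83. Exact McNemar rejects in 48% of trials at N=100 and 56% at N=120.
- Exponential rates: fall = 0.20×0.49 = 9.8 points; rejection 31% and 38%.

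For p from 0.20 to 0.40 across both versions, s = 10% gives 3.6 points (0.10×0.60²) to 8.0 points (0.10×0.80), and s = 30% gives 10.8 to 24.0 points. At s = 0 there is no fall and the test rejects in 3–4% of trials.

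**Step 2: simulation.** Poisson events with gamma-distributed rates (mean 0.4–0.7 per year, shape 0.7–1.0), n = 110. Triggered patients have an event in the 3 months before enrolment. Exact McNemar is counted only when it favours benefit.

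| Share triggered | Spurious fall (points) | McNemar declares benefit |
|---|---|---|
| 0% | about 0 | about 2% |
| 10% | 3–5 | 6–13% |
| 20% | 7–10 | 20–38% |
| 30% | 10–16 (49–59% before, 34–48% after) | 40–76% |

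**Step 3: what shrinks it.** These variations also rest on assumptions.

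- If only a fraction *q* of triggering events counts as related, the equal-risk fall becomes s·q·(1−p). At q = 0.5 and 30% triggered, with the rate of related events unchanged, 10–16 points becomes about 5–8, and McNemar declares benefit in about 10–21% of trials.
- If event rates rise 15% over follow-up, the 30% case gives about 7–12 points and 19–50%. The 10% case gives 0–2 points and 1–4%.

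**Step 4: do the planned analyses remove it?** No. McNemar's test compares the two discordant counts and cannot tell selection from effect. Baseline covariates take the same value for a patient in both periods, while the selecting event is itself the pre-period outcome. Adjusting for those covariates leaves the period contrast biased.

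**Step 5: does a lagged window help?** With a pre-window of months −15 to −3, pre and post agree within 0.3 points when all triggers lie in the last 3 months, and false benefit is 1–2%. That success is partly built in, because the gap covers exactly the trigger period. If triggers reach back 6 months, the same window leaves a 5–7 point fall and 10–20% rejection at 30% triggered. If risk rises 15%, it leans about 3 points against benefit.

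**The case against.** The article lists who refers, not what prompts referral, and gives no share per source. Of the sources named, only transitional care points to a recent discharge. Eligibility needs no acute event, sampling is consecutive, and Section 2.3 describes a proactive offer by telephone. This stands: a reader might infer that enrolment is often triggered by an acute event, but the article does not say so.

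A reader might also infer that any admission before referral scores as a pre-event. It does not. Section 2.5 limits the outcome to related causes, and Section 2.6 classifies hospitalizations by codes, discharge letters and, failing those, two general practitioners. An unrelated admission can prompt referral without counting. This stands too, and it shrinks the bias.

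Nor can one say that an inert intervention would be expected to show a significant fall. At 10% triggered, that happens in 6–13% of trials. Ageing and disease progression push the other way, and deaths after enrolment could push either way.

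Finally, Section 3 concedes the missing comparator and disclaims inference. That is a partial answer. Uncontrolled confounding and secular trends have no stated direction, whereas this bias does, and the effect size will still be reported.

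**Conclusion.** The point holds as an exposure of unknown size. The article fixes the abutting windows, the referral route, the single group and the tests. Together these let selection on recent related events inflate the pre-period, and the article neither names nor addresses it.

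Under no effect, the spurious fall runs from nothing, if no referral is event-triggered, to 10–16 points at 30% triggered. This assumes mean rates of 0.4–0.7 per year, constant risk, triggers within 3 months and every trigger counting as related. Relaxing the last assumption, or letting risk rise, reduces it. The documents do not support a claim that the bias will occur at a given size, or that it will exceed any real effect, since they give no trigger share, event rate or target effect. What they do support is that, as planned, a reader could not tell this artefact from benefit.

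**What to change.** 1. Keep the planned comparison of months −12 to 0 and pre-specify alongside it a McNemar analysis of the same binary composite with a lagged 12-month pre-window, for example months −15 to −3. Add a longer lag, such as −18 to −6, as a check. Each keeps a full year, so season stays balanced. Whether a lagged window should become the primary definition is debatable, since any one gap is arbitrary.
2. At enrolment, record the referral source and the date of the last ED visit or admission.
3. Show monthly event rates around enrolment, and report results separately for patients with and without a recent event.
4. Name regression to the mean in Section 3, and state in advance that a fall which disappears with the lagged window will not be attributed to the intervention.

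The cost is a wider date range in a data pull already planned from the regional database, two fields at enrolment and amended wording. No extra patients or visits are needed. The downsides are an older pre-period, which may lean slightly against benefit if risk rises with age, and residual bias if triggers lie further back than the gap. The windows should be fixed before outcome data are seen.

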### 2.3. Procedure

A logic model [21,22] has been developed to organize the intervention’s components and guide the development of the protocol (Figure 1). The model was developed following a systematic review of effective nurse-led interventions to manage chronic conditions in primary care [23] and a local qualitative study of patients with multimorbidity and their informal caregivers regarding their preferences and needs for current primary care nursing services. After a six-hour training program conducted by researchers across three sessions, nurses will deliver the experimental care to patients with chronic conditions. The intervention is rooted in the Chronic Care Model [4,24] and the Middle Range Theory of self-care in chronic illnesses [25,26]. This proactive approach will be proposed and explained to patients through an initial phone call. On this occasion, users who agree to participate will be scheduled for an appointment or a home visit, depending on their ability to reach the Community Health Home. Then, nurses will conduct an initial structured assessment with interviews and tools, and will set follow-ups to monitor self-care development and clinical conditions. Patients will receive at least three contacts over six months, alternating between in-person visits and phone calls. However, nurses can increase contact frequency when patients present with multiple educational needs or poor self-care skills.

### 2.4. Intervention

The intervention will be the only manipulated variable, as the nurses involved are the same that would have been leading care for patients and their informal caregivers within the Community Home. Nurses will conduct a therapeutic education program following standard components developed based on multiple frameworks, theories, and evidence, focusing on behavioral changes [27], enhancing engagement and empowerment [28,29], self-care and symptom management [25,26,30], and planning health promotion strategies [31].

Specifically, during the first interview, the nurse will collect the following data.

(a)Socio-demographic status and family network: age, sex, cohabitation status and designated caregiver(s).(b)Patient and caregiver’s priority needs, capturing concerns, difficulties, and expectations with open-ended questions.(c)Clinical condition: vital signs, BMI, diseases and related medications, civil disability status, medical exams, and blood tests.(d)Socio-educational needs, meaning the following:
Lifestyles, combining physical activity, sleeping quality, alcohol consumption, and smoking habits;Self-care skills, using the Patient Activation Measure (PAM) questionnaire [32];Clinical–social frailty, assessing the risk with the Sunfrail questionnaire [33].

Other specific questionnaires will be used whenever concerns or issues are faced. All questionnaires that will be administered are validated in Italian; for each patient, scores will be collected in a specifically designed Excel file. This spreadsheet will serve as electronic documentation, including questionnaires, automated scoring, a summary of active clinical and educational issues, a medication plan, and goals shared with the patient. These elements will be prefilled based on nurses’ data input and finalized manually. The tool will serve as a guide for nurses to deliver the intervention and will become part of the healthcare electronic system. All information will be incorporated into an educational plan, which will be provided to the patient in written form.

Throughout all interviews, four communication approaches will be implemented:(a)Teach-back [34,35]: This is a communication strategy designed to assess an individual’s understanding of newly acquired information. After presenting the information incrementally, the individual is asked to summarize what has been understood using their own words, thereby identifying any knowledge gaps. This approach actively engages the participant and holds the professional accountable for effective communication, ensuring that information is conveyed in small, manageable portions and comprehension is verified at each step.(b)Motivational Interviewing [36,37]: This is an evidence-based counseling style that facilitates a collaborative dialogue within a supportive and empathetic environment. This approach aims to elicit the individual’s intrinsic reasons for change and strengthen their commitment and motivation to achieve specific goals. The primary components include reflective listening, open-ended questions to elicit change-oriented statements, synthesis and support affirmations, and targeted information.(c)Sharing Evidence Routine for a Person-centered Plan for Action (SHERPA model) [38,39]: This is a structured three-phase shared planning approach. In Phase 1 (Share), the individual’s problems are identified collaboratively, including illnesses related to physical and emotional elements (diagnosis, behaviors, symptoms, concerns, emotions), social issues such as isolation or poverty, and challenges in disease management, aiming to create a person-centered problem framework rather than a diagnosis-focused one. In Phase 2 (Link), the professional and the patient discuss how to connect these issues, mapping them visually in circles of varying sizes proportional to their significance. Pathophysiological connections help the individual understand their condition, while the patient’s connections provide insights into personal values, beliefs, and non-clinical expectations. In Phase 3 (Plan), the professional and the individual prioritize these issues and set specific goals, such as reducing medication, managing symptoms, modifying unhealthy behaviors, or achieving social objectives.(d)Interviews with family units, inspired by the Calgary Family Assessment and Intervention Models [40]: These shift the focus away from the individual patient, are designed to support families as a unit, and are particularly effective when families experience physical and emotional distress and face challenges in response to stressful events such as death, end-of-life care, or acute and chronic illnesses. By employing a systematic approach to family assessment—investigating structural, developmental, and functional categories, along with genograms and ecomaps—the nurse can identify family strengths and resources within the caregiver network and formulate appropriate interventions. Such interventions may include providing information and perspectives, using questions to promote change in the affective, behavioral, and cognitive domains of family functioning, encouraging family members to assume or relinquish caregiving roles, and activating community and social resources to support the family.
